### 3.9. Sensitivity and Uncertainty Analysis

Deterministic sensitivity analyses will be conducted to assess the robustness of results to parameter uncertainty, including variations in (1) equipment costs (purchase vs. rental models), (2) therapist time costs, (3) discount rates (0% and 5% annually), and (4) utility mapping assumptions for historical controls. Probabilistic sensitivity analysis using Monte Carlo simulation (5000 iterations) will characterize joint parameter uncertainty and generate cost-effectiveness acceptability curves showing the probability of BCI being cost-effective across a range of willingness-to-pay thresholds. An additional scenario analysis will model partial supervision—approximately 25%, rather than 50%, of sessions unsupervised from the midpoint of training following initial orientation, acknowledging this proportion may vary in practice—to assess the minimum substitution level required for a favorable incremental cost-effectiveness ratio.

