### 2.4. Sample Size

Based on comparable feasibility studies in BCI stroke rehabilitation literature and recommendations from our recent meta-analysis [24], a sample of 10 subjects will be sufficient for this feasibility study. Accounting for a 20% dropout rate (*n* = 2), the final proposed sample size is 12 participants. Recruitment will aim to stratify the sample by stroke type in an approximate ratio of 40% hemorrhagic (ICH) to 60% ischemic (infarct) stroke, consistent with local case-mix.

This sample size follows established guidance for pilot and feasibility trials, in which the objective is to estimate feasibility parameters and their variability rather than to test efficacy; widely cited recommendations propose approximately 12 participants for pilot studies [35,36], and a sample of 10–12 is adequate to estimate a feasibility proportion of about 80% (for example recruitment or adherence) with a 95% confidence interval half-width of roughly ±20%. A formal efficacy-based power calculation is therefore not appropriate for the present feasibility endpoints. Nonetheless, to inform the design of a future definitive trial, an indicative a priori power calculation was performed in G*Power (version 3.1). Anchoring conservatively on 6 points—the lower end of the FMA-UE minimal clinically important difference range established largely in chronic stroke (4–6 points)—acute-stroke-specific estimates are reportedly higher, approximately 7–10 points, but 6 points was retained as a conservative estimate and the pooled effect implied by our meta-analysis (mean change 5.23 points, standard error 0.70; approximate standard deviation 3.4 in the analyzed cohorts) [24]; a two-sided paired within-group comparison (α = 0.05, power = 0.80) would require approximately 6–8 participants to detect a change of the minimal clinically important difference magnitude, whereas a two-arm parallel comparison designed to detect a 4-point between-group difference at an assumed standard deviation of 6 (Cohen’s d ≈ 0.67) would require approximately 37–46 participants per arm. The variance and recruitment-rate estimates generated by the present feasibility study will be used to refine these calculations and to power the subsequent randomized controlled trial.

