### 3.2. Economic Evaluation

An incremental cost–utility analysis (CUA) will be conducted alongside the feasibility study to generate exploratory cost data of BCI rehabilitation compared to standard care, acknowledging the limited precision afforded by the single-arm design. The economic evaluation will adopt a healthcare system perspective over a 24-week time horizon, consistent with the clinical follow-up period.

To keep the economic evaluation focused, it is organized around two scopes: (1) the within-trial 24-week cost–utility analysis from a healthcare-system perspective described above and (2) a secondary long-term extrapolation. For the latter, a cohort state-transition (Markov) model, structured around post-stroke functional health states (for example, FMA-UE severity together with functional dependency) and an absorbing death state, will project costs and quality-adjusted life years over 2-year and 5-year horizons, using an annual cycle with half-cycle correction and discounting at 3% per annum (0% and 5% in sensitivity analysis), consistent with Singapore health-technology-assessment norms. Transition probabilities and utilities will be derived from the trial, the TTSH registry, and the published literature; a societal perspective incorporating productivity losses and informal caregiver time will be explored as a sensitivity analysis rather than as a primary scope. As it remains uncertain whether clinical gains from BCI-rehabilitation are sustained into the chronic phase beyond the trial follow-up period, all estimates extrapolated beyond 24 weeks will be treated as exploratory and interpreted with caution. Structural and parameter uncertainty will be characterized through deterministic and probabilistic sensitivity analyses, reported in accordance with CHEERS 2022.

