### 3.3. Comparator Group: Historical Controls

Given the single-arm feasibility design, the comparator group will be derived from the TTSH stroke rehabilitation registry (2017–2025). Historical controls will be propensity-matched to BCI participants based on (1) baseline FMA-UE score, (2) age, (3) stroke type (hemorrhagic vs. ischemic), and (4) time post-stroke at rehabilitation admission (2–12 weeks). To reduce residual confounding, the propensity model will additionally include sex, baseline functional status (admission FIM and MBI), comorbidity burden (Charlson Comorbidity Index), clinically relevant concomitant medications (for example antispasticity and mood-active agents), the total inpatient rehabilitation therapy dose, and the calendar year (era) of admission. Historical control data will be obtained from an institutional inpatient stroke rehabilitation cohort assembled between 2022 and 2025 (more than 100 patients), for which baseline and discharge EQ-5D-5L utilities and FMA-UE scores are available to support propensity matching and quality-adjusted life year estimation. Corresponding inpatient rehabilitation cost data will be obtained from hospital administrative and costing databases. FMA-UE categories may use severe impairment (FMA-UE 0–19) and moderate-to-mild impairment (FMA-UE 20–47). This approach has been previously validated in the TTSH setting for evaluating upper extremity recovery outcomes [40]. Matching will be performed using nearest-neighbor propensity score matching with a caliper of 0.2 standard deviations to ensure adequate balance on baseline covariates. The matching ratio will be 1:3 (BCI/control) to maximize statistical power while maintaining adequate matching quality. Balance diagnostics will be assessed using standardized mean differences (target < 0.1 for all covariates) and variance ratios. To limit temporal confounding arising from the eight-year registry window (2017–2025)—over which ward staffing, rehabilitation protocols, and case-mix may have changed—the primary comparator analysis will be restricted to the contemporaneous 2022–2025 inpatient cohort, calendar year will be included as a matching and adjustment covariate, and models will additionally be fitted with admission era as a fixed effect; the influence of the matching window will be examined in sensitivity analyses that progressively restrict controls to narrower, more recent time bands. Sensitivity analyses will explore alternative matching specifications, including different caliper widths and matching algorithms (genetic matching, coarsened exact matching) to assess robustness of findings to matching choices. If precise stroke onset dates are unavailable for historical controls, hospital arrival date will be used as a proxy, consistent with Singapore Stroke Registry methodology.

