### 3.7. Cost-Effectiveness Analysis

The incremental cost-effectiveness ratio (ICER) will be calculated as the difference in mean costs between BCI and standard care groups divided by the difference in mean QALYs: ICER = (Cost_BCI—Cost_Control)/(QALY_BCI—QALY_Control). Results will be interpreted against the Singapore willingness-to-pay threshold of approximately SGD 50,000–100,000 per QALY gained. A secondary cost-effectiveness analysis will calculate the cost per point improvement in FMA-UE to provide clinically interpretable metrics alongside the cost-utility analysis.

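### The within-trial acceptability curve rests on a Monte Carlo parameter analysis alone; no stated method carries patient sampling error, the cost–QALY correlation or the matched sets, so the curve can err in either direction

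*Protocol article*

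**What the plan says.** Section 3.2 of the protocol article sets out two economic scopes. The first is "the within-trial 24-week cost–utility analysis from a healthcare-system perspective described above"; the second is a longer-term Markov extrapolation. The same paragraph closes with one statement on uncertainty: "Structural and parameter uncertainty will be characterized through deterministic and probabilistic sensitivity analyses, reported in accordance with CHEERS 2022".

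Section 3.7 defines the ICER as "the difference in mean costs between BCI and standard care groups divided by the difference in mean QALYs" and gives no interval method. QALYs come from each patient's EQ-5D-5L scores by area under the curve (3.6). Costs come from billed charges where available (3.5).

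The data are few: "the final proposed sample size is 12 participants" (2.4), and for the controls "The matching ratio will be 1:3 (BCI/control) to maximize statistical power while maintaining adequate matching quality" (3.3), so at most 36 controls.

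Section 3.9 lists deterministic variations in equipment cost, therapist time cost, discount rate and utility mapping. It then says: "Probabilistic sensitivity analysis using Monte Carlo simulation (5000 iterations) will characterize joint parameter uncertainty and generate cost-effectiveness acceptability curves". It does not say which of the two scopes this serves.

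**The concern.** A probabilistic sensitivity analysis propagates uncertainty in model inputs, which suits the Markov scope. In the within-trial scope, with 12 treated patients, a main source of uncertainty is which patients happened to be enrolled and matched. None of the inputs listed in 3.9 represents that.

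Two outcomes are possible. If the simulation varies only unit costs, discount rates and utility mapping, sampling error is left out. If it draws mean costs and mean QALYs from distributions, the answer depends on their covariance and on the matching, and the text mentions neither.

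The stake is the height and slope of the acceptability curve between SGD 50,000 and 100,000 per QALY (3.7). Readers will take that curve as the probability that BCI is cost-effective, and section 4 expects the economic data to inform resource allocation.

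**Working it through.** The article gives no standard error, interval or acceptability probability, so there is no figure to reproduce. The check asks how far the result moves if the structure is lost.

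**Inputs from the article:** 12 participants (2.4); three controls each (3.3); threshold λ of SGD 50,000 to 100,000 per QALY (3.7).

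**Assumptions, not in the article:** cost SD σc = SGD 8,000; QALY SD σq = 0.08; cost–QALY correlation ρ from −0.6 to +0.6; within-set correlation r from 0 to 0.4, the same for cost and QALY.

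**Step 1, variance of one patient's net benefit.** v = λ²σq² + σc² − 2λρσcσq.

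At λ = 50,000, λσq = 4,000. In millions, v = 16 + 64 − 64ρ = 80 − 64ρ.

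**Step 2, variance of mean incremental net benefit with 12 sets of 1:3.** Var = (v/12)·[1 − 2r + (1 + 2r)/3] = (v/9)·(1 − r).

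With ρ = 0 and r = 0 (independent draws, matching ignored), SE = √(80 million/9) = SGD 2,981.

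**Step 3, correct SE divided by the independent-draw SE.** At λ = 50,000 this is √[(1 − 0.8ρ)(1 − r)].

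| What is lost | Calculation | Ratio |
|---|---|---|
| ρ = −0.6 only | √1.48 | 1.22 |
| ρ = −0.3 only | √1.24 | 1.11 |
| ρ = +0.3 only | √0.76 | 0.87 |
| ρ = +0.6 only | √0.52 | 0.72 |
| r = 0.1 only | √0.90 | 0.95 |
| r = 0.4 only | √0.60 | 0.77 |
| ρ = −0.3 and r = 0.2 | √(1.24 × 0.80) | 1.00 |
| ρ = −0.6 and r = 0.2 | √(1.48 × 0.80) | 1.09 |
| ρ = −0.6 and r = 0.4 | √(1.48 × 0.60) | 0.94 |

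A ratio above 1 means that independent draws give a curve that is too sharp; below 1, too flat. At λ = 100,000, λσq = 8,000 and v = 128 − 128ρ in millions, so ρ = −0.6 alone gives √1.6 = 1.26.

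**Step 4, effect on the curve.** Where independent draws give an acceptability probability of 0.90 (z = 1.2816) at λ = 50,000, the correct value is Φ(1.2816/1.217) = 0.854 at ρ = −0.6, r = 0. At ρ = +0.6, r = 0.4 the ratio is √(0.52 × 0.60) = 0.559, and the correct value is Φ(1.2816/0.559) = 0.989.

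**Step 5, simulation at λ = 50,000.** For each combination of ρ (−0.5, −0.3, 0, +0.3) and r (0, 0.2, 0.4), 1,500 trials were simulated, with 400 bootstrap resamples of whole matched sets in each. Independent draws gave 0.85 to 1.49 times the true SE. The matched-set bootstrap gave 0.93 to 1.00 times. Theory for 12 sets is √(11/12) = 0.957, so the plain bootstrap is about 4% narrow.

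**Step 6, number of iterations.** The Monte Carlo error of a probability from 5,000 draws is at most √(0.25/5,000) = 0.7 percentage points. The iteration count is not the problem.

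**The case against.** The strongest reply is that section 3.9 does not say that costs and QALYs are drawn independently, names no distributions, and speaks of joint uncertainty. Mean incremental cost and mean incremental QALY could be simulated with a covariance estimated from the patients, and such detail is commonly left to an analysis plan, which is not shown. This stands as far as it goes. A reader might infer that the simulation will be parametric with independent draws; the article does not say so, and the sizes above apply only if the structure is in fact lost. The point does not rest on missing detail, though. The article fixes the method that produces the curve, and that method addresses parameter uncertainty, not patient sampling.

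A reader might also infer that the curve will be too sharp, because patients who do badly tend to cost more and gain less. The documents do not support a fixed direction. They give no cost–QALY correlation, a positive one has the opposite effect, losing positive within-set correlation makes the curve too flat, and the two losses can cancel.

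The control data may also not be complete patient pairs. Section 3.3 describes control utilities at baseline and discharge, and 3.6 allows mapped values. Resampling alone does not carry mapping uncertainty, so Monte Carlo methods keep a place here. This stands and is reflected in the fix.

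Finally, 3.2 and 3.10 call the economic results exploratory and preliminary, and no decision rule in the article depends on the curve. That lowers the importance. It does not supply a valid interval.

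**Conclusion.** The point holds in limited form. For the within-trial scope, the only named source of the acceptability curve is a parameter simulation, and no stated method carries sampling error, cost–QALY pairing or matching. If they are lost, the error at a threshold of SGD 50,000 runs from a standard error that should be about 22% larger (correlation −0.6, no within-set correlation) to one that should be 5–23% smaller (within-set correlation 0.1–0.4 alone). A positive cost–QALY correlation moves it further in the second direction. These sizes rest on assumed SDs and correlations. Neither independent sampling nor a curve that is too sharp is established. The primary feasibility outcomes are not affected.

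**What to change.** In section 3.9, separate the two scopes.

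- **Within-trial scope:** take the net-benefit interval and the acceptability curve from a non-parametric bootstrap of 5,000 resamples. The unit is the matched set: one participant with that participant's controls, each patient's cost and QALY kept together. Apply a small-sample correction for 12 sets, for example scaling the bootstrap SE by √(12/11) = 1.044. A joint cost–QALY model that respects the matching would serve equally well.
- **Monte Carlo analysis:** keep it for the Markov model. For the within-trial scope, layer unit-cost and utility-mapping uncertainty on the bootstrap, since control utilities may be mapped or incomplete.

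The cost is a few sentences and a short program, with no new data or visits. The stated precision may change slightly, in a direction that cannot be known beforehand. With 12 sets the results stay exploratory under either method.

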### 3.5. Cost Perspective and Therapy Time Differential

The BCI intervention is modeled as additional adjunctive therapy in addition to standard of care rather than a substitute for standard care. Under this assumption (Scenario A), BCI participants receive 30 min of BCI training plus 60 min of standard occupational therapy per session (90 min total), whereas standard care patients receive approximately 60 min of occupational therapy per session based on TTSH rehabilitation protocols [40]. The incremental cost of BCI therefore includes both equipment-related costs and the additional 30 min of therapist time per session. Where available, actual billed charges from hospital administrative databases will be used to estimate healthcare costs. For intervention-specific costs not captured in routine billing (e.g., BCI equipment depreciation, additional therapist time), unit costs will be derived from institutional costing data. This pragmatic approach balances data availability with accuracy of cost estimation. A sensitivity scenario modeling partial substitution—approximately 25%, rather than 50%, of within-session supervision withdrawn from the midpoint of the training course following an initial supervised orientation period, noting this proportion may vary in practice—will be examined to explore conditions under which a favorable ICER may be achievable.

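### Section 3.9 sets out to find the minimum substitution level for a favourable ICER but specifies only one level, about 25%, which by itself shows only whether 25% is enough

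*Protocol article*

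**What the plan says.** Section 3.9 (Sensitivity and Uncertainty Analysis) describes a scenario with "approximately 25%, rather than 50%, of sessions unsupervised from the midpoint of training following initial orientation". Its purpose is "to assess the minimum substitution level required for a favorable incremental cost-effectiveness ratio". The only flexibility offered is the remark "acknowledging this proportion may vary in practice".

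Section 3.5 (Cost Perspective and Therapy Time Differential) describes what appears to be the same scenario as "approximately 25%, rather than 50%, of within-session supervision withdrawn from the midpoint of the training course", with the aim "to explore conditions under which a favorable ICER may be achievable".

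The deterministic analyses listed in Section 3.9 vary equipment cost, therapist time cost, discount rate and utility mapping. The level of supervision is not among them. Section 3.7 defines the ICER as the difference in mean cost over the difference in mean QALYs, and reads it against roughly SGD 50,000 to 100,000 per QALY. Section 3.9 does not say which end of that range makes an ICER favourable.

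**The concern.** A minimum required level has to be found by varying the level or by solving for it. Section 3.9 as written does neither. If the ICER is favourable at 25%, a smaller share might also have been enough. If it is unfavourable at 25%, that run alone does not show whether a larger share would do. In both cases the stated quantity is not among the stated outputs.

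The two sections also differ in aim (finding a minimum versus exploring conditions) and in unit (sessions versus supervision within sessions). Neither says plainly what the 25% is a percentage of. Two analysts following the text could therefore cost different scenarios under the same label.

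At stake is the usefulness of one exploratory economic output, which the Discussion presents as an opening step towards less closely supervised and remote delivery. No feasibility benchmark, safety rule or clinical outcome depends on it.

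**Working it through.** The plan gives no ICER, unit cost or QALY gain for this scenario, so there is no figure to reproduce. The check uses the plan's session counts and its ICER definition.

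**Inputs from the protocol article**
- Up to 15 sessions (Section 2.6). All 15 are assumed delivered.
- 30 added therapist minutes per session (Section 3.5), so 15 × 30 = 450 added minutes.
- Midpoint at 7.5 sessions, leaving 7.5 × 30 = 225 minutes after it.

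**What 25% removes**
- 25% of post-midpoint sessions (wording of 3.9): 0.25 × 7.5 × 30 = 56.25 minutes, and 56.25/450 = 12.5%. If 7 or 8 whole sessions follow the midpoint, the result is 52.5 or 60 minutes (11.7% or 13.3%).
- 25% of supervision within each post-midpoint session (wording of 3.5): 0.25 × 30 × 7.5 = 56.25 minutes, which is the same.
- 25% of all 15 sessions, taken from the second half: 0.25 × 15 × 30 = 112.5 minutes, and 112.5/450 = 25%.
- Upper limit, all supervision withdrawn after the midpoint: 225/450 = 50%.

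The choice of denominator therefore changes the scenario by a factor of two. The choice between sessions and within-session supervision does not change it on these figures.

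**What a threshold analysis would solve**

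Let s be the share of post-midpoint supervision withdrawn, c the therapist cost per minute, E all other incremental cost, dQ the QALY gain and λ the willingness to pay. Assume that dQ does not depend on s. Then

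ICER(s) = [E + c(450 − 225s)] / dQ.

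Incremental net benefit, λ·dQ − [E + c(450 − 225s)], is zero at

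s* = (E + 450c − λ·dQ) / (225c).

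**Illustration with assumed inputs** (none is in the document): E = SGD 500, c = SGD 2 per minute, dQ = 0.02.

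| s | ICER (SGD per QALY) |
|---|---|
| 0% | (500 + 900)/0.02 = 70,000 |
| 25% | (500 + 787.5)/0.02 = 64,375 |
| 50% | (500 + 675)/0.02 = 58,750 |
| 100% | (500 + 450)/0.02 = 47,500 |

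- At λ = 50,000: s* = (500 + 900 − 1,000)/450 = 0.89. The 25% run on its own says only that s* is above 25%.
- At λ = 100,000: s* = (1,400 − 2,000)/450 = −1.33, so no substitution is needed.
- The 25%-of-all-sessions reading equals s = 50% here, so the labelled scenario would report 58,750 instead of 64,375.

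Over assumed ranges of E = 500 to 2,000, c = 1 to 2 and dQ = 0.01 to 0.03, s* runs from below 0 (already favourable) to above 1 (not reachable). For example, E = 2,000, c = 2, dQ = 0.02 and λ = 50,000 give (2,900 − 1,000)/450 = 4.22.

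**The case against.** The strongest reply is that the threshold can be recovered from what is planned. If cost is linear in the withdrawn share and QALYs do not depend on supervision, the fully supervised base case and the 25% run fix a straight line. In the illustration the ICER falls by 5,625 per 25 percentage points, or 22,500 over the full range. So (70,000 − 50,000)/22,500 = 0.89, the same answer. Section 2.6 also commits to reporting the cost of extra therapist time separately from device costs, which supplies the main cost inputs. This stands. A reader might infer that the plan cannot deliver a threshold at all, and the documents do not support that. What remains is that the article states neither the two assumptions nor the solving step.

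A second reply is that a condensed article may leave the set of modelled levels to a fuller plan, with 25% as an anchor. That is arguable, since the text does not say that only one level will be run. But it does state both the aim and the analysis, and they do not match. The remark about variation in practice is a caveat, not a range.

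Third, a reader might infer that the two descriptions of the 25% give different costs. On the plan's 30 added minutes per session they give the same 56.25 minutes. The ambiguity that matters is the denominator.

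Finally, the economic work is labelled exploratory with n = 12, and the Discussion leaves remote delivery to later research. It would overstate the matter to say that an adoption decision turns on this run. That limits the weight of the point, not its correctness.

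**Conclusion.** The point stands in a modest form. Section 3.9 states a threshold aim and specifies one level, which by itself shows only whether about 25% is enough. Sections 3.5 and 3.9 differ in aim and in unit, and leave the denominator open. The scenario removes 12.5% of the added therapist time if 25% refers to post-midpoint sessions and 25% if it refers to all sessions, assuming all 15 are delivered. The monetary illustration rests on assumed inputs and shows only that the threshold can lie below, inside or above the feasible range. Severity is low: a worthwhile clarification to an exploratory cost scenario, with no effect on the primary feasibility outcomes.

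**What to change.** In Section 3.9, commit to varying or solving for the unsupervised share from 0 to 100% after the midpoint. Report the share at which incremental net benefit reaches zero at SGD 50,000 and at SGD 100,000 per QALY, or state that no share does so. Keep 25% as a labelled point on that curve.

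State what is assumed about QALYs when supervision is reduced, since the result depends on it whichever way the threshold is obtained. Use one definition and one denominator for the share in Sections 3.5 and 3.9.

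If a threshold is not wanted, reduce the aim in Section 3.9 to the exploratory one already in Section 3.5 and still reconcile the definitions.

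The cost is a sentence or two of text and a loop, or one closed-form line, in a model that will exist anyway. No new data are needed. This concerns the cost model only and implies nothing about which supervision level is appropriate.
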